**Table 5 Classification of the severity of the laboratory adverse events.**

| **Adverse event** | **Grade 1** | **Grade 2** | **Grade 3** | **Grade 4** |
| --- | --- | --- | --- | --- |
| Hemoglobin decrease compared to baseline - gm/dL | 0.1 – 1.5 | 1.6 – 2.0 | 2.1 – 5.0 | >5.0 |
| Hemoglobin (women) - gm/dL | 11.0 – 12.0* | 9.5 – 10.9 | 8.0 – 9.4 | <8.0 |
| Hemoglobin (men) - gm/dL | 12.5 – 13.5* | 10.5 – 12.4 | 8.5 – 10.4 | <8.5 |
| Leukocytosis – cell/mm3 | 10,800^†^– 15,000 | 15,001 – 20,000 | 20,001 – 25,000 | >25,000 |
| Leukopenia – cell/mm3 | 2,500 – 3,500* | 1,500 – 2,499 | 1,000 – 1,499 | <1,000 |
| Lymphopenia – cell/mm3 | 750 – 1,000* | 500 – 749 | 250 – 499 | <250 |
| Neutropenia – cell/mm3 | 1,000 – 1,499* | 500 – 999 | 300-499 | <300 |
| Platelets Decreased – cell/mm3 | 125,000 – 140,000* | 100,000 – 124,000 | 25,000 – 99,000 | <25,000 |
| Creatinine – mg/dL | 1.5^†^ – 1.7 | 1.8 – 2.0 | 2.1 – 2.5 | >2.5 or requires dialysis |
| ALT/AST – increase by factor | 1.1 – 2.5 x ULN | 2.6 – 5.0 x ULN | 5.1 – 10 x ULN | >10 x ULN |
| Bilirubin – when accompanied by any increase in ALT/AST – increase by factor | 1.1 – 1.25 x ULN | 1.26 – 1.5 x ULN | 1.51 – 1.75 x ULN | >1.75 x ULN |
| Bilirubin – when ALT/AST are normal – increase by factor | 1.1 – 1.5 x ULN | 1.6 – 2.0 x ULN | 2.0 – 3.0 x ULN | >3.0 x ULN |

ILN: inferior limit of the normal range.

ULN: upper limit of the normal range.

* If the ILN is less than the upper limit of Grade 1, the ILN will be used as an upper limit to Grade 1.

^†^ If the ULN is greater than the lower limit to Grade 1, the ULN will be used as a lower limit to Grade 1.

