- Have received blood products in the past 6 months, including transfusions or immunoglobulin, or scheduled administration of blood products or immunoglobulin for the first 28 days after vaccination
- Any other condition that might put at risk the safety/rights of a potential participant or his/her compliance with this protocol in investigator’s opinion or his representative physician
- Laboratory values at screening equal to or greater than Grade 2 will be considered to be exclusionary. Vital signs may be performed up to three times to allow for transient conditions to resolve. Screening laboratory values that are out of range, but are considered to be due to an acute illness or process may be repeated once. Grade 1 laboratory values will be reviewed by a licensed study clinician and the clinician will determine whether the laboratory abnormality is clinically significant and should be considered exclusionary. If determined to be clinically insignificant, the study team is not required to follow the laboratory until resolution or the value is determined to be clinically stable.

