### 9.3.8 Procedures for Out-of-range Laboratory Test Values

Out-of-range laboratory values and AEs. To the extent possible, all reference ranges for clinical laboratory test results will be pre-specified. The site staff will follow the Toxicity Table (Table 5). Laboratory values that are out-of-range will not be considered an AE unless they qualify as a Grade 2 or above on the Toxicity Table. The reference ranges for the laboratory will be taken in to consideration when determining out of range results.

Out-of-range test values may be considered an SAE if two circumstances are met:

1. the value rises to the level of Potentially Life-threatening (Grade 4), and
2. the event is determined by the Principal Investigator to pose an immediate risk of death.

A Grade 4 laboratory result does not, in and of itself, constitute an SAE. Grade 4 places a laboratory value as a potentially life-threatening event, but a Grade 4 laboratory result should not be reported as an SAE unless the PI has determined that it does, in fact, pose an immediate risk of death.

Assessing relatedness and clinical significance of out-of-range laboratory values: All laboratory results should be reviewedAny laboratory finding Grade 2 and above is regarded as an AE. The investigator will assess relatedness and clinical significance for these findings.

Clinical judgment always should be used to determine whether a laboratory result requires additional follow up. However, the investigator should redraw any Grade 2 or above laboratory result that is deemed clinically significant at an unscheduled visit to check if the result has normalized.

Any Grade 2 or above laboratory value that is clinically significant and has not returned to normal or stabilized by day V2+194 should be marked by the investigators as “continuing” or “unresolved.” The investigator should assure that the participant is referred for appropriate medical follow-up, if indicated.

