**After the first 100 subjects enrolled:**

- - 8% or more participants who received at least one study injection to date experience severe (Grade 3/4) study injection-related local reaction of the same category other than measured erythema or induration.
  - 4% or more participants who received at least one study injection to date experience a severe (Grade 3/4) study injection-related systemic reaction of the same category (excluding laboratory AEs, which will be monitored separately).
  - 2% or more participants who received at least one study injection to date experience a severe (Grade 3/4) study injection-related abnormality in the same laboratory parameter.

These halting rules refer to adverse reactions suspected to be vaccine related.

Butantan retains the right to temporarily suspend or prematurely discontinue this study at any time related to safety. If the study is stopped or suspended prematurely, Butantan will inform the local principal investigator as well as regulatory authorities about the decision and the reasons for termination or suspension. If such action is taken, all efforts must be made to ensure the safety of the participants enrolled in the study. The principal investigator will assist Butantan in informing the responsible IRB/ethics committee and provide the reason for the suspension or termination. In case of premature study or study clinic closure, the monitor will conduct all activities as indicated in the Clinical Monitoring Plan.

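### Table 5 gives bilirubin of 2.0 x ULN (ALT/AST normal) both Grade 2 and Grade 3; some ALT/AST, bilirubin and platelet bands do not meet if results are read more finely than printed

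*Protocol*

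**What the plan says.** Table 5 (section 9.3.2) grades laboratory results from 1 to 4. The rows that matter here are:

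- Bilirubin, ALT/AST normal, Grades 1 and 2: "1.1 – 1.5 x ULN | 1.6 – 2.0 x ULN". Grades 2 and 3: "1.6 – 2.0 x ULN | 2.0 – 3.0 x ULN".
- ALT/AST, Grades 1 to 3: "1.1 – 2.5 x ULN | 2.6 – 5.0 x ULN | 5.1 – 10 x ULN".
- Platelets in cell/mm3, Grades 2 and 3: "100,000 – 124,000 | 25,000 – 99,000". Grade 1 starts at 125,000.

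The footnotes to Table 5 adjust only the outer limit of Grade 1. Section 8.2.1 leaves normal ranges to each clinical laboratory, and section 4 has the study physician assign the grade.

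The grades are then used in three places:

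- Screening (section 5.3): "Laboratory values at screening equal to or greater than Grade 2 will be considered to be exclusionary".
- Adverse-event status (section 9.3.8; section 9.1 agrees): "Laboratory values that are out-of-range will not be considered an AE unless they qualify as a Grade 2 or above on the Toxicity Table".
- Halting (section 9.6): in the first 100 subjects, three or more participants with a related Grade 3 abnormality, or two or more with Grade 4, in one parameter. After that, 2% or more who "experience a severe (Grade 3/4) study injection-related abnormality in the same laboratory parameter".

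**The concern.** A grading scale should give each result exactly one grade. The bilirubin row fails this at 2.0 x ULN, where the top of Grade 2 is also the bottom of Grade 3. One site may count the result as severe and another may not, and the laboratory halting rules count severe results.

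The other rows raise a weaker question. Their adjacent limits differ by 0.1 x ULN or by 1,000 cells, and the protocol does not say whether a result is rounded before it is compared. If it is not, values between the bands have no grade. A gap between Grades 1 and 2 leaves exclusion and adverse-event status open. A gap between Grades 2 and 3 leaves the halting count open. The trial has at least three sites and site-specific normal ranges, so different local habits could give different grades to equivalent results.

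**Working it through.** **Inputs.** The band limits come from Table 5 and are read as closed intervals. The protocol gives no ULN, so these are assumptions: ALT/AST 35 to 56 U/L and bilirubin 1.0 to 1.3 mg/dL, reported to 0.01 unless stated.

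**1. The overlap (bilirubin, ALT/AST normal).** Grade 2 is 1.6 to 2.0 and Grade 3 is 2.0 to 3.0, so the shared value is 2.0 x ULN.

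- ULN 1.0: 2.0 x 1.0 = 2.0 mg/dL.
- ULN 1.2: 2.0 x 1.2 = 2.4 mg/dL.
- ULN 1.3: 2.0 x 1.3 = 2.6 mg/dL.

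If the ratio is first rounded to one decimal, every ratio from about 1.95 to 2.05 becomes 2.0 and takes both grades. At ULN 1.2 that is about 2.35 to 2.45 mg/dL. Rounding makes the overlap larger.

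Comparable rows step on at this point: creatinine goes from 2.0 to 2.1, and leukocytosis from 15,000 to 15,001.

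**2. The gaps, comparing the exact result.**

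| Row | Between grades | Limits | Example with no grade |
|---|---|---|---|
| ALT/AST | 1 and 2 | 2.5 / 2.6 x ULN | ULN 40: 100 and 104, so 101-103 U/L |
| ALT/AST | 2 and 3 | 5.0 / 5.1 x ULN | ULN 40: 200 and 204, so 201-203 U/L |
| Bilirubin, ALT/AST normal | 1 and 2 | 1.5 / 1.6 x ULN | ULN 1.0: 1.51-1.59 mg/dL; ULN 1.2: 1.81-1.91 mg/dL |
| Platelets | 1 and 2 | 125,000 / 124,000 | 124,001-124,999 cell/mm3 |
| Platelets | 2 and 3 | 100,000 / 99,000 | 99,001-99,999 cell/mm3 |

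For ALT/AST, the ULNs tried from 35 to 56 leave 3 to 5 whole-unit results ungraded at each boundary. Platelets have 999 + 999 = 1,998 ungraded whole numbers. None of these three rows has a gap between Grades 3 and 4.

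**3. The gaps, comparing at the printed precision.** With ratios rounded to one decimal and platelets reported in whole thousands, every gap in the table above closes. The gaps therefore depend on reporting precision; the overlap does not.

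**4. Which decision each defect can reach.**

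| Defect | Exclusion at screening | AE status | Grade 3 halting count |
|---|---|---|---|
| Bilirubin 2.0 x ULN, Grade 2 or 3 | no, either grade excludes | no, either grade is an AE | yes |
| Gaps between Grades 1 and 2 | yes | yes | no |
| Gaps between Grades 2 and 3 | not the issue: the gap lies above the Grade 2 band | not the issue: the gap lies above the Grade 2 band | yes |

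**5. Size of the halting counts.** The limit after the first 100 is the smallest whole number not below 0.02 x n. For n = 101 this is 2.02, so 3. For n = 150 it is 3.00, so 3. For n = 200 it is 4. For n = 432 it is 8.64, so 9. In the first 100 the Grade 3 limit is 3. One participant's grade can decide such a count, but only when the others needed have already occurred.

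**The case against.** Several points on the other side are sound.

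- **Printed precision.** Limits such as 2.5 and 2.6 are commonly read at the precision shown. The protocol does the same elsewhere: creatinine 1.7/1.8 in Table 5, and fever 38.4/38.5 °C and erythema 50/51 mm in Table 4. A reader might infer that Table 5 simply leaves values ungraded. The document does not support that without a condition, because comparison at the printed precision closes the gaps. What remains is that no such rule is stated, and that the leukocytosis row, also in cell/mm3, runs to the single cell while the platelet row does not.
- **Reach of the overlap.** A reader might infer that it also disturbs eligibility and adverse-event status. It does not, because Grade 2 and Grade 3 have the same consequence for both.
- **Halting needs more than a grade.** The result must also be judged related and be in the same parameter as the others, and a trigger leads to ad hoc DSMB review. That limits how often the defect matters, and the protocol gives no basis for a frequency.
- **Clinical review at screening.** Section 5.3 allows exclusion for a clinically significant Grade 1 value or any other condition of concern, so a borderline value is still looked at. This does not settle adverse-event status.
- **Other documents.** A rounding convention may sit in the analysis plan or data management plan, which are not shown. That could answer the gaps. Rounding cannot answer the overlap, which is in the protocol's own table and is applied in real time.

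The statement below Table 6 that the worst severity is used might seem to break the tie. It concerns the course of an event until it resolves, not a single value with two grades.

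The row for bilirubin with raised ALT/AST, "1.1 – 1.25 x ULN | 1.26 – 1.5 x ULN | 1.51 – 1.75 x ULN | >1.75 x ULN", also has steps of 0.01 x ULN. They are too narrow to matter much, and nothing here rests on them.

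**Conclusion.** The overlap is certain and needs no assumption: 2.0 x ULN in one bilirubin row has two grades, at the limit for severe counts and laboratory halting. It is one exact value per laboratory range, or about 1.95-2.05 x ULN if ratios are rounded to one decimal.

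The gaps are conditional. They exist only where results are compared more finely than the printed limits, and the examples in U/L and mg/dL rest on assumed ULNs. They also depend on reporting precision: with bilirubin reported to one decimal and a ULN of 1.2, only 1.9 mg/dL stays ungraded. Where they exist, the Grade 1/2 gaps bear on exclusion and adverse-event status, and the Grade 2/3 gaps bear on halting.

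Few results will be affected. The correction is still worth making, because a decision threshold is ambiguous as written and costs almost nothing to repair.

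**What to change.** 1. Reconcile the row for bilirubin with normal ALT/AST so that 2.0 x ULN belongs to one grade only. Which side takes it is for the sponsor to decide.
2. For ALT/AST, bilirubin and platelets, either make adjacent bands contiguous, with each boundary assigned explicitly to one side, or state the precision at which results and ratios are compared. If rounding is chosen, step 1 must come first, because rounding widens the overlap.
3. Apply the same rule at every site. Deriving the grade centrally in the data capture system from the value and the site's ULN is one way to do so, but it is optional: section 4 assigns grading to the study physician, and a clear table would serve.

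The cost is a wording change in one table and, if wanted, one derivation. No new data are needed.

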**Table 6 Classification of the severity of the unsolicited clinical adverse events.**

| **Adverse event** | **Grade 1** | **Grade 2** | **Grade 3** | **Grade 4** |
| --- | --- | --- | --- | --- |
| Clinical adverse event (as defined by this protocol) | Does not interfere  with daily activities | Mild interference with daily activities | Prevent daily activities | Emergency department visit*  OR  Hospitalization |

* It requires 12 hours or more of admission to a ward or emergency department for the management of the adverse event.

All cases of death will have their severity classified as Grade 4.

The worst severity reported to an adverse event, until its resolution or conclusion, will be the severity used to perform the study analysis.

### 9.3.3 Causal relationship classification

All adverse events should have their causal relationship to the investigational product classified by the principal investigator or a medical officer, following the adapted classification of the "Uppsala Monitoring Centre" of the World Health Organization (WHO-UMC), described in (Table 7). The sponsor may request additional clarification from the principal investigator to justify the causal relationship attributed to the event.

A causal relationship may also be revised at the request of the DSMB following a written justification.

**Table 7 Classification of the causal relationship of the adverse events to the investigational product**

| **A reasonable causal relationship** | | | **A causal relationship NOT reasonable** | |
| --- | --- | --- | --- | --- |
| The Adverse Event is considered an Adverse Reaction | | | The Adverse Event cannot be considered an Adverse Reaction | |
| **Certain** | **Probable** | **Possible** | **Unlikely** | **Not related** |
| A clinical event, including a laboratory test abnormality (abnormal value) with a plausible temporal relationship to the administration of the intervention; | A clinical event, including a laboratory test abnormality (abnormal value) with a reasonable temporal relationship to the administration of the intervention; | A clinical event, including a laboratory test abnormality (abnormal value) with a reasonable temporal relationship to the administration of the intervention; | A clinical event, including a laboratory test abnormality (abnormal value) that due to the timing of the administration of the intervention has an unlikely relationship, but not impossible; | A clinical event, including a laboratory test abnormality (abnormal value) that due to the timing of the administration of the intervention has no relationship; |
| It cannot be explained by a concurrent disease or other intervention or medication;  The event must be definitive pharmacologically or phenomenologically (i.e., is an objective and specific disorder or a pharmacologically recognized phenomenon); | It is unlikely to be attributed to a concomitant disease or other medication or intervention; | It can also be explained by a concurrent disease or other medication or interventions; | Another disease or another medication provides a plausible explanation. | Another disease or another medication provides a plausible explanation. |
| The response to an interruption or withdrawal is plausible (pharmacologically, pathologically); | The response to the interruption or withdrawal is clinically reasonable; | There is a lack of information or lack of clarity about the withdrawal or interruption of treatment. |  |  |
| A satisfactory rechallenge procedure if necessary. | A rechallenge procedure is not necessary. |  |  |  |

### 9.3.4 Solicited Reactogenicity (Expected Reactions)

Immediate Reactions (within 30 minutes)

All participants will be observed for 30 minutes after administration of study product, with appropriate medical treatment readily available in case of an anaphylactic reaction following the administration of study product. Immediate reactions will be assessed by a study physician or appropriately trained medical staff. All reactions that occur during this time will be recorded on the CRF. Any immediate reaction which meets the criteria for an SAE must also be documented on an SAE form.

Emergency medicines will be available at the study clinic to be ready to give first aid if any adverse reactions or events should occur among any participant participating in this research.

### 9.3.5 Solicited Local and Systemic Reactions

Specific local and systemic reactions will be solicited (specifically asked of participants) while participants are in the study. These specific reactions, which are signs and symptoms, will be graded by a study clinician using the Toxicity Table for Grading Adverse Events (see Toxicity Tables 4, 5, 6). Grading will use predefined scales based on functional assessment or magnitude of reaction, where available. Where grading scales are not provided, the reaction will be graded for severity based on interference with participant functionally, as for all other AEs (see Section 9.3.2). Severity of redness, swelling and induration at the injection site should always be graded based on size.

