# Study Outcome Measures (Endpoints)

## 3.1 Safety Endpoints

**Primary Endpoints:** The vaccine safety profiles will be assessed according to:

- Number, severity and percentage of participants with solicited and/or unsolicited local and/or systemic adverse reactions during a 7-day period post each vaccination.

**Secondary Endpoints:** The following safety parameters will be followed:

- Number and percentage of participants with unsolicited adverse reactions for 28 days post each vaccination.
- All serious adverse events (SAEs) occurring over the study period.

**Exploratory Endpoints:** The following safety parameters will be followed:

- All adverse events of special interest (AESIs) as listed in Annex A occurring over the study period.

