# Assessment of Safety and Adverse Events

## 9.1 Definition and Categorization of AEs

The primary objective of this study is to evalute the safety profile and immunogenicity of the vaccine candidates. An AE (adverse event) is defined as any untoward medical occurrence in a participant administered an study product, which may or may not bear a causal relationship with this study injection. An AE can therefore be any unfavorable and unintended sign (including an abnormal laboratory finding), symptom, or disease temporally associated with the use of a medicinal product, whether or not considered related to the medicinal product. A subset of AEs, those commonly observed after influenza vaccine administration are described in the Participant Diary and will be specifically requested for 7 days post each study injection. Those AEs are termed “solicited” and will be evaluated for potential relationship with study product. Out-of-range laboratory abnormalities observed after study injections will be graded according to the grading table (see Table 5) and their clinical significance and potential relationship to study product assessed. Only those laboratory abnormalities greater than Grade 1 will be recorded as AEs.

All AEs should be graded using the Tables for Grading AEs (Tables 4, 5 and 6). These tables contain list of specific clinical and laboratory safety measurements of interest to the study. All clinical safety evaluations must be made by a qualified physician.

Any clinical sign or symptom or laboratory finding at any time-point might be categorized as an SAE if it meets the criteria established.

All adverse events will be MedDRA coded.

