### 9.3.2 Severity of Event

The severity of the solicited clinical adverse events (local and systemic), laboratory events and unsolicited AEs will be classified by a numeric scale ranging from 1 to 4, according to Table 4, 5, 6, created based on the FDA guidance.^[[22]](#endnote-23)^

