**Table 4 Classification of the severity of the solicited clinical adverse events.**

| **Solicited Local Adverse Events** | | | | |
| --- | --- | --- | --- | --- |
| **Adverse Event** | **Grade 1** | **Grade 2** | **Grade 3** | **Grade 4** |
| Pain/tenderness at the injection site of the investigational product | Does not interfere  with daily activities | Repeated use of non-narcotic analgesic >24 hours  OR  Mild interference with daily activities | Any use of a narcotic analgesic  OR  Prevent daily activities | Emergency department visit*  OR  Hospitalization |
| Erythema at the injection site of the investigational product ^†^ | 25 – 50 mm | 51 – 100 mm | >100 mm | Necrosis  OR  Exfoliative dermatitis |
| Swelling/Induration at the injection site of the investigational product ^†^ | 25 – 50 mm | 51 – 100 mm  OR  Mild interference with daily activities | >100 mm | Necrosis |
| Ecchymosis at the injection site of the investigational product ^†^ | 25 – 50 mm | 51 – 100 mm | >100 mm | Necrosis |
| Pruritus at the injection site of the investigational product | Does not interfere  with daily activities | Mild interference with daily activities | Prevent daily activities | Emergency department visit*  OR  Hospitalization |
| **Solicited Systemic Adverse Events** | | | | |
| Nausea/vomiting | Does not interfere  with daily activities  OR  1 to 2 episodes in 24 hours | Mild interference with daily activities  OR  More than 2 episodes in 24 hours | Prevent daily activities, it requires IV hydration | Emergency department visit*  OR  Hospitalization  OR  Hypovolemic shock |
| Fever | 37.8 – 38.4°C | 38.5 – 38.9°C | 39.0 – 40.0°C | >40°C |
| Chills | Slight cold sensation; chills, teeth chatter | Moderate chills in the entire body, it requires the use of narcotics | Serious or prolonged, no response to narcotics | ----- |
| Headache | Does not interfere  with daily activities | Repeated use of non-narcotic analgesic >24 hours  OR  Mild interference with daily activities | Any use of a narcotic analgesic  OR  Prevent daily activities | Emergency department visit*  OR  Hospitalization |
| Fatigue/malaise | Does not interfere  with daily activities | Mild interference with daily activities | Prevent daily activities | Emergency department visit*  OR  Hospitalization |
| Myalgia | Does not interfere  with daily activities | Mild interference with daily activities | Prevent daily activities | Emergency department visit*  OR  Hospitalization |

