| Arthralgia | Does not interfere  with daily activities | Mild interference with daily activities | Prevent daily activities | Emergency department visit*  OR  Hospitalization |

* It requires 12 hours or more of admission to a ward or emergency department for the management of the adverse event.

^†^ The value recorded should be measured at the largest diameter and as a continuous variable.

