**Local reactions:**

- Size of erythema (at site of injection) in cm
- Size of swelling/ induration (at site of injection) in cm
- Pain/Tenderness (at site of injection)
- Pruritus (at site of injection)
- Eccymosis (at site of injection) in cm

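### Section 9.3.5 grades swelling and induration always on size, but Table 4 also makes them Grade 2 for mild interference at any size

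*Protocol*

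**What the plan says.** **Rule in the text.** Section 9.3.5 says: "Severity of redness, swelling and induration at the injection site should always be graded based on size". The same section says that solicited reactions "will be graded by a study clinician using the Toxicity Table for Grading Adverse Events (see Toxicity Tables 4, 5, 6").

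**Rule in the table.** In Table 4, the swelling/induration row gives Grade 1 as 25–50 mm, Grade 2 as "51 – 100 mm OR Mild interference with daily activities", Grade 3 as above 100 mm, and Grade 4 as necrosis. The erythema and ecchymosis rows use the same size bands for Grades 1 to 3 and have no interference alternative.

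**Authority of the table.** Section 9.1 says "All AEs should be graded using the Tables for Grading AEs (Tables 4, 5 and 6"). Section 9.3.2 says severity "will be classified by a numeric scale ranging from 1 to 4, according to Table 4, 5, 6". No sentence says which rule prevails if Table 4 and the size sentence in 9.3.5 differ.

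**Use in the analysis.** The primary safety endpoint in section 3.1 is "Number, severity and percentage of participants with solicited and/or unsolicited local and/or systemic adverse reactions during a 7-day period post each vaccination". Section 9.2 lists swelling/induration among the solicited local events. The note below Table 6 takes the worst reported severity into the analysis, and section 11.5 summarises events by severity.

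**Injection arm.** Section 6.2.1 has the two doses given in alternating arms. Section 6.2.2 (item 3) requires the non-dominant arm, and the visit procedures in 7.2.1 (item 10, first dose) and 7.2.5 (item 7, second dose) both say the same.

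**The concern.** A clinician with a participant whose swelling is small but mildly limits daily activities has two written instructions that give different answers. Both are part of the grading rules for a primary safety endpoint in which severity is counted. Grading is done by clinicians at a minimum of three sites, so different people may settle the conflict differently.

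At stake is the consistency of the swelling rows in the reactogenicity tables: how many participants are Grade 1, how many are Grade 2, and how many have any graded swelling at all. A table chosen afterwards cannot make graders consistent with each other, so the rule is best settled before grading begins.

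**Working it through.** The protocol gives no figure for this event, so there is none to reproduce. The check has two parts: the grade under each rule, and the weight of one participant.

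**1. Grade by diameter for swelling with mild interference.** Inputs are the size bands and the interference alternative in Table 4, and the size sentence in 9.3.5. The Table 4 grade is taken as the worse of the size grade and Grade 2 for interference.

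| Largest diameter | By size (9.3.5) | By Table 4 | Agree? |
|---|---|---|---|
| Below 25 mm | No grade | Grade 2 | No |
| 25–50 mm | Grade 1 | Grade 2 | No |
| 51–100 mm | Grade 2 | Grade 2 | Yes |
| Above 100 mm | Grade 3 | Grade 3 | Yes |

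Without interference the two rules agree at every diameter in the table. The disagreement is therefore confined to swelling of 50 mm or less with mild interference. In the 25–50 mm band it moves a participant between Grade 1 and Grade 2. Below 25 mm it moves a participant between ungraded and Grade 2, so the any-grade percentage changes too.

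Grade 4 is outside the table above because necrosis is not a size. Read with complete literalness, the size sentence could never yield Grade 4.

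**2. Weight of one participant.** Arm size is 54 (section 11.1 and Table 3). A pooled adjuvant group is 3 × 54 = 162.

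- One arm: 1/54 = 1.85%, or 1.9 percentage points.
- Pooled adjuvant group: 1/162 = 0.62%, or 0.6 percentage points.

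With the exact (Clopper-Pearson) 95% intervals that section 11.2 specifies, a Grade 2 swelling count of 0/54 has the interval 0 to 6.6% (upper limit 1 − 0.025^(1/54) = 0.066). A count of 1/54 has 0.05% to 9.9%. One regraded participant moves the estimate by much less than the width of either interval.

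**3. Halting rules.** The percentage and count triggers for local reactions in section 9.6 use only Grade 3/4 and exclude measured erythema or induration. The disagreement found in step 1 lies at Grade 2 and below, so it does not reach them. Necrosis at the injection site associated with product administration is a separate trigger at one participant, whatever grade it is given.

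**4. Direction.** Section 5.4.2 blinds the personnel who make assessments after injection, and section 5.4.1 stratifies randomisation by site. A grader's preference for one rule therefore cannot follow the allocation.

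**The case against.** The best defence is that the two passages can be read together. Section 9.3.5 says severity is based on size, not on size alone. The sentence just before it sends reactions without a scale to a grading by interference, so the size sentence may only be meant to keep measurable signs out of that fallback. The section also accepts scales built on function or on magnitude. Table 4 itself has a non-size criterion in the same row, necrosis at Grade 4, so strict size-only grading cannot be the whole intention. A clinician who measures the diameter and then reads the grade from Table 4 could claim to follow everything.

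Much of this stands. Table 4 is probably the intended authority, and the size sentence is the outlier. It does not remove the conflict. The sentence names swelling and induration and says always. The Grade 2 alternative in Table 4 is functional, carries no size condition, and is absent from the erythema and ecchymosis rows that the protocol otherwise bands in the same way. A careful grader could defend either result.

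Two stronger readings are tempting, and the protocol supports neither.

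- **Lost information.** The Table 4 footnote says "The value recorded should be measured at the largest diameter and as a continuous variable", and the list in 9.3.5 has only "Size of swelling/ induration (at site of injection) in cm" for this reaction. A reader might infer that interference will not be recorded for swelling, so that a Table 4 grade could never be rebuilt. But that list also mentions no interference for pain or pruritus, which Table 4 grades on interference. It is a list of reactions, not a data specification, and the diary and case report form are not shown.
- **Likely frequency.** A reader might apply the event rates in Table 8 to this event and conclude that disagreement is likely in an arm. Those rates are generic. Nothing in the protocol says how often small swelling with mild interference occurs, so such a calculation would show no impact.

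**Conclusion.** The conflict is real and stands in the current text. For swelling or induration of 50 mm or less with mild interference, Table 4 gives Grade 2, and the size sentence gives Grade 1 or no grade. The Grade 1 and Grade 2 counts, and the any-grade percentage, for this one sign within the primary reactogenicity endpoint can therefore depend on the grader.

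The effect is minor. Each affected participant moves an arm's Grade 2 rate by 1.9 points. How many would be affected is unknown, because the protocol gives no rate. Given blinded assessment, the result is noise between graders and sites rather than bias between arms. No halting decision depends on it, and nothing in the protocol shows that the choice of a candidate would.

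It would go too far to say that Grades 3 and 4 are identical under both rules. On the strictest reading of the size sentence, necrosis could not be graded at all. That is one more reason to let Table 4 govern.

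The conclusion assumes that the worst applicable Table 4 criterion sets the grade. The inconsistency over the injection arm is a separate slip, and no effect on reaction counts is claimed for it.

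**What to change.** **Preferred.** Reword the size sentence in 9.3.5 so that swelling and induration are graded by Table 4, as 9.1, 9.3.2 and the rest of 9.3.5 already direct. This also keeps necrosis as Grade 4. Check that the diary and case report form capture interference with daily activities for swelling/induration, and add one item if they do not.

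**Alternative.** Delete the interference alternative from the Grade 2 cell of the swelling/induration row in Table 4, which brings that row into line with erythema and ecchymosis for Grades 1 to 3.

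**Injection arm.** Remove the reference to alternating arms from 6.2.1, so that it agrees with 6.2.2, 7.2.1 and 7.2.5.

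The cost is a few words in each place and at most one diary or case report form item. Visits, sample size and analysis do not change.
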